### Sample size

The required sample size has been set at 128 participants; allowing for a 13 % loss to follow-up at 18 months post randomisation, a total of 148 patients will need to be recruited. To reach this target, we will need to identify 290 eligible patients: the recruitment rate observed in a surgical trial involving THR recently conducted in the coordinating centre was 51 % with an attrition rate of 13 % [21].

A sample size of 128 patients will provide 80 % power to test that one surgical approach is superior to the other approach 18 months post randomisation by 10 points on the WOMAC Index, equivalent to a 0.5 standard deviation difference. The significance level for this superiority hypothesis is set at 5 % (two-sided).

Although it is known that infection following total joint replacement reduces patient satisfaction and seriously impairs functional health and quality of life, there is no published research on the likely difference in patient-reported outcomes between patients undergoing one-stage and two-stage revision for PJI. The standard deviations observed prior to one-stage or two-stage revision surgery for WOMAC global and sub-indices range between 18 and 25 [22, 23].

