The primary outcome is the continuous WOMAC Index collected at 18 months postrandomisation. The primary analysis will consist of a generalised linear mixed model (GLLM) with identity link function regressing baseline and 18-month WOMAC measures on the treatment indicator (one-stage treatment versus two-stage treatment), measurement point (baseline versus 18-months) and their interaction (treatment × measurement point). This will be a two-level hierarchical GLLM (measurements within patients). As the treatment allocation is stratified by hospitals and participants are nested within a small number of hospitals, the primary analysis will also be adjusted for indicators of hospital centre introduced as fixed effects (using the coordination centre as a reference). The intervention effect will be assessed using appropriate contrast to identify the mean difference in WOMAC at 18 months and due emphasis will be put on the associated 95 % confidence interval and the *p* value resulting from the Wald-test associated with this contrast. The primary analysis will be based on the intention-to-treat principle, analysing participants in the groups to which they were randomised. All individuals with a WOMAC Index observed at baseline and/or at 18 months will be considered for this analysis. The GLLM with identity link function is based on a likelihood method, which provides unbiased estimation under the missing at random hypothesis despite the presence of missing outcome information. Various sensitivity analyses will be conducted to adjust for imbalance baseline characteristics between treatment groups, assess the clustering at surgeon level or investigate the impact of missing data using various imputation strategies. Finally a per-protocol analysis will be conducted.

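### As ordinarily fitted, the two-level primary model assumes equal WOMAC variance at baseline and 18 months, so the primary p value and confidence interval are mis-sized if the variances differ

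*Protocol article*

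**What the plan says.** The Statistical analysis section of the protocol article sets out the primary model in some detail. It is a "generalised linear mixed model (GLLM) with identity link function regressing baseline and 18-month WOMAC measures on the treatment indicator", together with "measurement point (baseline versus 18-months) and their interaction (treatment × measurement point"), and with hospital indicators as fixed effects. On the hierarchy it says: "This will be a two-level hierarchical GLLM (measurements within patients").

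On the estimate it says: "The intervention effect will be assessed using appropriate contrast to identify the mean difference in WOMAC at 18 months". Emphasis falls on the 95% confidence interval and the p "value resulting from the Wald-test associated with this contrast". The analysis set is broad: "All individuals with a WOMAC Index observed at baseline and/or at 18 months will be considered for this analysis". The section describes the model as likelihood-based, "which provides unbiased estimation under the missing at random hypothesis despite the presence of missing outcome information".

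The section names no random-effects structure, residual covariance, robust standard error or degrees-of-freedom method. The sensitivity analyses it lists concern baseline imbalance, clustering by surgeon and missing data. The Sample size section gives a planning difference of 10 points (0.5 SD) and SDs of 18 to 25 observed before revision surgery, across the global score and the subscales. It gives no SD at 18 months.

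**The concern.** Each patient has at most two measurements. A two-level model of measurements within patients is ordinarily fitted as a patient random intercept plus one residual variance, and with one residual variance and two occasions a random slope cannot be identified as well. The fitted covariance is then compound symmetry, with one variance shared by both occasions.

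Nothing in the article supports that equality. Baseline scores come from patients with an infected hip awaiting revision. The 18-month scores will mix patients who have recovered with patients who have not. The spread could be wider or narrower.

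The primary inference is at stake. If WOMAC is more variable at 18 months than at baseline, the standard error is too small and the test too liberal. If it is less variable, the test is conservative and power is given up. The covariance also sets how a baseline value informs a missing 18-month value, so the statement about unbiasedness under missing at random depends on it as well.

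**Working it through.** **Inputs from the article.** Two-sided 5% level, 80% power, 10 points = 0.5 SD, 128 evaluable patients in a 1:1 ratio, 13% loss, 148 recruited; pre-operative SDs of 18 to 25.

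**Assumed.** Every 18-month SD, and a baseline to 18-month correlation r = 0.4 where one is needed. The article gives neither.

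**The plan's own figure.** The planning SD is 10/0.5 = 20. Per arm, n = 2(1.960 + 0.842)²/0.5² = 62.8 by the normal approximation and 63.8 by the t-test, so 64 per arm and 128 in total. Then 128/0.87 = 147.1, rounded up to 148. The stated sample size is reproduced.

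**Effect of a common variance.** Take complete pairs and separate arm-by-time means, ignoring the hospital terms. The contrast is the difference between arms in mean 18-month WOMAC. Write s0 and s18 for the SDs at baseline and 18 months, and n for the patients per arm.

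- True SE = s18 × √(2/n)
- SE under a common variance = √[(s0² + s18²)/2] × √(2/n)
- SE ratio R = √[(s0² + s18²)/2] / s18
- Actual type I error = 2[1 − Φ(1.96 R)]; actual coverage = 1 minus this

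Example, 20 then 22: (400 + 484)/2 = 442, √442 = 21.02, R = 21.02/22 = 0.956, type I error 6.1%.

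| Baseline SD / 18-month SD (18-month assumed) | R | Type I error | Coverage of 95% CI |
|---|---|---|---|
| 20 / 20 | 1.000 | 5.0% | 95.0% |
| 20 / 22 | 0.956 | 6.1% | 93.9% |
| 22 / 20 | 1.051 | 3.9% | 96.1% |
| 18 / 22 | 0.914 | 7.3% | 92.7% |
| 22 / 18 | 1.117 | 2.9% | 97.1% |
| 18 / 25 | 0.871 | 8.8% | 91.2% |
| 25 / 18 | 1.210 | 1.8% | 98.2% |

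**Power at 25/18.** True SE = 18 × √(2/64) = 3.18. With the common variance, power for 10 points is Φ(10/3.18 − 1.96 × 1.210) = 78.0%. With the 18-month variance it is Φ(10/3.18 − 1.96) = 88.2%.

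**Simulation check.** REML fits with 74 per arm, 20 of 148 missing at 18 months completely at random, seven centres as fixed effects, r = 0.4 and 2,000 runs per case gave these type I errors:

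| SDs | Common variance | Separate variances |
|---|---|---|
| 20 / 20 | 5.4% | 5.5% |
| 20 / 22 | 6.1% | 5.4% |
| 22 / 20 | 3.4% | 4.6% |
| 18 / 25 | 10.9% | 6.0% |
| 25 / 18 | 1.3% | 4.8% |

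Simulation error near 5% is about 0.5 percentage points (√(0.05 × 0.95/2000)). The direction agrees with the closed form throughout. At 18/25 the separate-variance fit also came out at 6.0%, so the whole excess of 10.9% over 8.8% should not be laid on the common variance.

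**Missing 18-month values.** A patient with only a baseline score contributes through the implied slope of 18-month on baseline WOMAC. At 18/25 and r = 0.4 the covariance is 0.4 × 18 × 25 = 180. The true slope is 180/324 = 0.556, and the common-variance slope is 180/474.5 = 0.379. If the 13% lost differ from completers by an assumed 10 baseline points, the arm's 18-month mean shifts by (0.556 − 0.379) × 0.13 × 10 = 0.23 points. This cancels in the contrast if both arms lose similar patients. If the losses differ by 10 points in opposite directions, it reaches 0.46 points, against a target of 10.

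**The case against.** A reader might infer that the protocol forces equal variances. It does not. The article nowhere says random intercept, compound symmetry or common residual variance, and a two-level model can carry a separate residual variance at each occasion or robust standard errors. Covariance structure is commonly left to the SAP, which is not shown, and an unstructured covariance would contradict nothing in the article. This part stands: the equal-variance model is the ordinary fit of what is written, not a stated restriction.

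A reader might also infer that the p value is seriously wrong whenever the variances differ. The figures do not support that. The quoted 18 to 25 are all pre-operative and mix the global score with subscales, so they say nothing about change over time. Putting opposite ends of that range at the two occasions gives an outer bound, and the direction is unknown. With equal variances the test is exact, and a 10% difference in SD moves the error by about one percentage point. In the worst conservative case, power of 78.0% is close to the planned 80%. What is lost there is the gain that a smaller 18-month SD would have brought.

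Nor does the unbiasedness claim collapse. The bias computed above is small even in an outer case, and imputation-based sensitivity analyses are planned.

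What the objection does not remove is that the article positively chooses this model and this Wald inference, names no safeguard against unequal variances, and states the unbiasedness property without its condition. A better specification is available at almost no cost.

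**Conclusion.** The point holds as a moderate one. The primary model as ordinarily fitted makes an equal-variance assumption that the article does not support. If the assumption fails, the primary test and interval are mis-sized. For a 10% SD difference the type I error is about 6.1% or 3.9%; at the outer cases it is about 8.8% or 1.8%. All of this depends on assumed 18-month SDs, and the direction cannot be told from the article.

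With complete pairs the estimated treatment difference is unchanged, so only the standard error is in question. With missing 18-month data the estimate can move too, but by a few tenths of a point under the assumptions shown.

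A second, related weakness adds to the case for change. With treatment, time and their interaction all free, the 18-month contrast on complete pairs is not baseline-adjusted, although baseline is in the model. The precision that baseline WOMAC could provide is therefore given up.

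**What to change.** State in the SAP, before outcome data by arm are seen, that the primary model estimates the baseline and 18-month variances separately with a free correlation (an unstructured 2×2 covariance), fitted by REML. This keeps everyone with a value at either occasion, as the article intends. The unbiasedness statement should then carry its condition: missing at random and a correctly specified model.

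Preferably, also constrain the baseline means to be equal across arms, by dropping the treatment main effect and keeping time and the treatment-by-time term, so that the contrast is baseline-adjusted. The separate variances should accompany this, because the adjustment uses the fitted covariance even with complete pairs. ANCOVA on 18-month WOMAC is an alternative, but a complete-case version would drop patients with only one measurement. At an assumed r = 0.4, adjustment multiplies the standard error by √(1 − 0.16) = 0.917. With SD 20 and 64 per arm, the SE falls from 3.54 to 3.24 and power rises from 80.7% to about 87%.

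The cost is one extra variance parameter (three instead of two), one option in the model code and a sentence or two of text. The 128 evaluable and 148 recruited patients, the data collection and the conduct of the trial are unchanged. If the SAP already specifies separate variances or robust standard errors, the main point is met and only the baseline adjustment and the wording of the unbiasedness claim remain.

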### Randomisation

After patients have been consented to the trial and have agreed to be randomised, preoperative outcome measures will be collected. They will then be randomly allocated to one of the two treatment groups (one-stage or two-stage revision surgery) in a 1:1 ratio. Randomisation within blocks of varying size will be conducted separately for each hospital. Block sizes will not be disclosed.

Randomisation will take place as close as possible to the time of surgery (maximum 12 weeks prior to surgery), whilst allowing sufficient time to plan the operation and order necessary equipment.

The randomisation sequence will be generated centrally by computer, and administered via the Internet by the Bristol Randomised Trial Collaboration.

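### The primary model lets the arms differ freely at baseline, so its 18-month contrast makes almost no use of baseline WOMAC; a common baseline mean would add precision at no cost.

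*Protocol article*

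**What the plan says.** The Statistical analysis section of the protocol article describes the primary model as "regressing baseline and 18-month WOMAC measures on the treatment indicator (one-stage treatment versus two-stage treatment), measurement point (baseline versus 18-months) and their interaction". It adds: "This will be a two-level hierarchical GLLM (measurements within patients"). Baseline WOMAC is therefore a response and not a covariate, and treatment appears as a main effect. The quantity to be reported is fixed: "The intervention effect will be assessed using appropriate contrast to identify the mean difference in WOMAC at 18 months".

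The only covariate adjustment named for the primary model is hospital: "the primary analysis will also be adjusted for indicators of hospital centre introduced as fixed effects". The analysis set is broad: "All individuals with a WOMAC Index observed at baseline and/or at 18 months will be considered for this analysis".

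The Randomisation section gives the order of events: "preoperative outcome measures will be collected. They will then be randomly allocated to one of the two treatment groups". The Blinding section confirms that patients learn their allocation only once the preoperative assessments are done.

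The Sample size section plans 128 evaluable patients (148 recruited, 13% loss) for 80% power to detect 10 points, equal to 0.5 SD, at two-sided 5%. It uses no baseline to 18-month correlation.

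**The concern.** A model that contains both the baseline and the 18-month score is easily taken to be adjusted for baseline. This one, in effect, is not. Its fixed effects (treatment, occasion, interaction) give each of the four arm-by-occasion cells its own mean. The 18-month contrast then depends on the two 18-month cells, and the baseline scores tell the model almost nothing about it.

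Baseline is measured before allocation, so the two arms have the same expected baseline mean by design. The parameter for a baseline difference estimates something known to be zero, and estimating it uses up the information that baseline WOMAC could have supplied. At stake are the width of the primary confidence interval and the part of any chance baseline difference that remains in the headline result. The Health economic analysis section already adjusts its primary analysis for preoperative WOMAC, so the trial team regards it as a relevant covariate there.

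**Working it through.** **Inputs.** From the Sample size section: difference 10, SD 10/0.5 = 20, 128 evaluable (64 per arm), two-sided 5%, 13% loss. From the Statistical analysis section: the model and contrast above. Assumed, because the documents do not give it: the baseline to 18-month correlation r, shown from 0.1 upwards. Also assumed: equal SDs at the two occasions.

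**1. The plan's own figure.** The SE of a difference in means is 20 × √(2/64) = 3.54. The noncentrality is 10/3.54 = 2.83, and the two-sample t-test with 126 degrees of freedom gives power 80.1%. Then 128/0.87 = 147.1, rounded up to 148. Both stated numbers reproduce, as those of an unadjusted comparison.

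**2. What the contrast estimates.** Write the mean as b0 + b1·treatment + b2·occasion + b3·treatment × occasion. The baseline difference is b1 and the 18-month difference is b1 + b3. With complete pairs and no centre terms, b1 + b3 equals the raw difference in 18-month means. A mixed-model fit to a simulated data set of 128 pairs gave 14.1178 by both routes. With seven centres as fixed effects and complete pairs, 2,000 simulated trials at each r gave a correlation above 0.999 between the contrast and the raw difference.

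**3. Empirical SEs, complete data, seven centres.**

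| r | Raw difference | Protocol model | Common baseline mean | ANCOVA |
|---|---|---|---|---|
| 0.3 | 3.52 | 3.51 | 3.37 | 3.38 |
| 0.5 | 3.51 | 3.52 | 3.06 | 3.07 |
| 0.7 | 3.50 | 3.50 | 2.51 | 2.51 |

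**4. With 13% missing at 18 months.** Patients with a baseline value only help the protocol model a little. Relative to completers, its variance factor is 1 − 0.13r²:
- r = 0.3: 1 − 0.13 × 0.09 = 0.988
- r = 0.5: 1 − 0.13 × 0.25 = 0.968
- r = 0.7: 1 − 0.13 × 0.49 = 0.936

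That is a gain of about 1–6%. Baseline adjustment has the factor 1 − r²: 0.91, 0.75 and 0.51. Simulating 148 randomised at r = 0.5 gave SEs of 3.52 (raw), 3.46 (protocol model), 3.01 (common baseline mean) and 3.06 (ANCOVA).

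**5. What using baseline is worth.** Replace SD 20 by 20√(1 − r²) with 64 per arm and the same t-test. The equivalent increase in sample size is 1/(1 − r²) − 1.

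| r | SE | Power | Equivalent extra patients |
|---|---|---|---|
| 0 (as planned) | 3.54 | 80.1% | – |
| 0.1 | 3.52 | 80.5% | 1% |
| 0.2 | 3.46 | 81.7% | 4% |
| 0.3 | 3.37 | 83.7% | 10% |
| 0.4 | 3.24 | 86.5% | 19% |
| 0.5 | 3.06 | 90.0% | 33% |

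**6. Chance imbalance.** With equal SDs, a chance baseline difference D shifts the expected unadjusted 18-month difference by r × D. If D = 5 and r = 0.4, the shift is 2 points. Under baseline adjustment it is about zero.

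**The case against.** The strongest reply is that nothing here is invalid. Under randomisation the contrast is unbiased. The sample size was set for an unadjusted comparison and the analysis delivers the power it promises. The article gives missing outcome data as its reason for a likelihood model, and claims adjustment only for centre. All of this stands. A reader might infer bias or a power shortfall, and the documents support neither.

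The size of the gain also rests on an assumed r. Baseline is taken in an infected hip before major surgery and the outcome comes 18 months after randomisation, so a low correlation cannot be excluded. At r = 0.1–0.2 the gain is worth only 1–4% more patients. This stands too, and is why the low end is shown.

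Other stronger readings are tempting but go too far:
- **Baseline contributes nothing at all.** This is exact only with complete 18-month data and no centre terms. The analysis set admits patients with baseline only, who recover a little variance.
- **A chance baseline difference enters the estimate in full.** It enters in proportion to r, and the unadjusted confidence interval already allows for that variation.
- **The result may be a change score.** The article names the 18-month mean difference, not the interaction, so power figures for a change score do not apply.
- **A single centre effect shared by both occasions distorts the result.** Allocation is 1:1 in blocks within each hospital, so centre is nearly balanced between arms. No material effect has been shown.
- **Covariates will be picked from the data.** The article does say "Various sensitivity analyses will be conducted to adjust for imbalance baseline characteristics between treatment groups", but this is a sensitivity analysis, and its covariate list may properly be left to the SAP, which is not shown.

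**Conclusion.** The point holds as one of forgone efficiency. Apart from centre adjustment and a variance gain of about 1–6% from baseline-only patients (13% loss, r 0.3–0.7), the primary estimate is the difference in 18-month means without adjustment for baseline WOMAC. It remains valid and meets its 80% target. Using baseline would bring power to between 80.5% (r = 0.1) and 90.0% (r = 0.5), and would remove the part of a chance baseline difference that now stays in, about r times that difference.

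The figures rest on SD 20, 64 per arm, a true difference of 10 points, equal SDs at both occasions, and an r that the documents do not supply. The direction is the same for any nonzero r. The point would fall only if the full analysis plan sets the baseline treatment effect to zero; the published model lists treatment as a main effect.

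**What to change.** Remove the treatment main effect from the primary model, so that both arms share one baseline mean and treatment enters only through its effect at 18 months (a constrained longitudinal model). This is justified because baseline WOMAC is collected before allocation. Keep the 18-month mean difference, the centre fixed effects and the analysis set as they are.

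Regressing 18-month WOMAC on treatment, baseline WOMAC and centre gives nearly the same precision (SE 3.06 against 3.01 at r = 0.5 with 13% loss). It drops patients with baseline only, however, and so departs from the stated analysis set. The constrained model is preferred.

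The cost is one line in the protocol or SAP, with no new data and no more patients. The sample size need not change: 128 evaluable patients remains sufficient for the stated power, and any gain from baseline is a margin on top.

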### Health economic analysis

We will conduct an intention-to-treat cost-effectiveness analysis from a societal perspective with costs to the NHS reported and analysed separately. All costs will be reported in 2018/2019 prices, and discounting will be applied as appropriate.

Health service resource use will be valued using hospital finance department and routine UK data [24, 25]. Social service, patient and informal carer resource use will be valued using routine [25, 26] and self-reported data.

The net monetary benefit statistic, using the difference in costs and the difference in quality-adjusted life years (QALY) between groups, and adjusted for hospital centre, baseline values (e.g. preoperative WOMAC, EQ-5D-5 L) and any covariate imbalance, will be calculated for different values of societal willingness to pay for a QALY. This will be the primary economic analysis.

The secondary economic analysis will examine the difference in costs with the differences in the WOMAC Index. If no arm is dominant, i.e. does not have statistically significant improved WOMAC Index and lower costs, then an incremental cost-effectiveness ratio will be estimated and cost-effectiveness acceptability curves will be derived using bootstrapping techniques. These will show the probability of the intervention being cost-effective at a range of ‘willingness to pay’ thresholds.

Sensitivity analysis will account for uncertainty and imprecision in measurements including multiple imputation models for missing values.

